#### Cost and Cost-Effectiveness Analyses (CEA)

Following similar studies of methods to increase mammography screening, we will conduct the analysis from the perspective of the payer/provider, FCHP/FC [55,56], rather than from the perspective society typically advocated by cost-effectiveness guidelines. Our rationale is that provider costs are the most relevant measure for groups considering adopting the study interventions. Separate comparisons will be conducted for each intervention year including calculating total startup costs for the ETTC and the RC group; calculating the cost of operating each intervention by summing costs for each intervention in each of the four intervention years. Costs for ETTC and RC will be calculated by amortizing startup costs across the four-year intervention period and adding the operating costs in each year of the intervention. Costs for RL intervention will be based on operating costs only. Recent cancer screening studies have compared differences in total, rather than average, costs across interventions [55-57]. To estimate the incremental cost-effectiveness of each intervention combination, we will compare the difference in the percentage of eligible women with mammograms divided by the difference in total cost for each intervention pair. We will report initial results as the incremental cost of increasing on-time mammograms by 1%. This figure can also be converted to an estimated cost per additional mammogram for a hypothetical sample of women. We will conduct sensitivity analyses to determine the effect of including or excluding startup costs, excluding administrative overhead costs, amortizing startup costs over a longer or shorter period, higher or lower (e.g. 10%) costs for each intervention and higher or lower effectiveness (e.g. 5% and 10% variation.)

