### Interventions

Only women ≥ 18 months from a mammogram receive study interventions. See Figure 2. When women are ≥ 18 months from their last mammogram, they all receive the same reminder letter. The letter is electronically signed by a woman's PCP and states: 1) there is no record of a mammogram in the last 18 months, 2) getting regular mammograms every 1-2 years is important and 3) her PCP recommends that she call the Study Scheduler for a mammogram appointment. When women call, the Study Scheduler uses the same script for all, except as noted below for women in the counseling arm. (See Table 2 for Study Scheduler Protocol)

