### Outcomes

The primary outcome is the proportion of women continuously enrolled for ≥24 months who have had ≥1 mammogram in the last 24 months. This measure mimics the standard HEDIS (Healthcare Effectiveness and Data Information Set) measure used by most health plans and systems to track mammography utilization, although the HEDIS measure is usually applied only to women age 50-69. The measure is a cross-sectional, prevalence measure that can be applied in a series of static "snapshots" to a dynamically changing population like the one in our study and in any typical health plan.

The secondary outcomes are 1) the number of women in each arm requiring repeat interventions and 2) the immediate outcomes (change in stage of readiness, mammography scheduling for those in the RC and ETTC arms during calls) and short term outcomes (receiving a mammogram within 3 months) following the interventions, for all women receiving the interventions for the first time, adjusted as needed by appropriate covariates (e.g. age, time to last mammogram, marital status and other factors).

The main cost-effectiveness outcome is the incremental cost-effectiveness of each intervention combination, that is, the difference in the percentage of eligible women with mammograms divided by the difference in total cost for each intervention pair. The study also measures separately the startup and operating costs of each intervention.

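### The planned cost per additional mammogram is really a cost per additional woman up to date, and the protocol does not allow the difference to be signed or sized

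*Protocol article*

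**What the plan says.** All references are to the protocol article.

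- **Effect measure.** In Outcomes, the primary measure is the "proportion of women continuously enrolled for ≥24 months who have had ≥1 mammogram in the last 24 months". The same section calls it a cross-sectional prevalence measure, taken as repeated snapshots of a changing population.
- **Ratio.** Under Cost and Cost-Effectiveness Analyses, "we will compare the difference in the percentage of eligible women with mammograms divided by the difference in total cost for each intervention pair". The result is reported the other way up, as incremental cost per 1% rise in on-time mammograms.
- **Conversion.** The next sentence reads: "This figure can also be converted to an estimated cost per additional mammogram for a hypothetical sample of women". No formula is given.
- **Cost period.** "Separate comparisons will be conducted for each intervention year". A year's cost is that year's operating cost plus, for RC and ETTC, a share of start-up cost spread over four years.
- **Trigger.** In Interventions, "Only women ≥ 18 months from a mammogram receive study interventions".
- **Data held.** Data Collection and Management lists mammogram dates among the data required for the primary outcome.

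**The concern.** A woman enters the share once, whether she had one mammogram in the window or two. Multiplying a percentage-point gain by a number of women therefore gives women, and dividing cost by it gives cost per additional woman up to date. Calling that a cost per additional mammogram changes the unit without stating the assumption needed.

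The design gives reasons to doubt that assumption. A woman who reaches the 18-month trigger is still inside the 24-month window and already counts. Contacting her costs money and may bring her next mammogram forward without moving the share. Secondary Outcomes Analyses hypothesizes that fewer ETTC than RC women will need a repeat telephone intervention, and compares completion within 19 months of the index mammogram. The plan thus expects the call arms to differ in how early women return, which the share does not record.

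At stake is a figure that potential adopters could use for budgeting or for comparison with other programs. Incremental cost-effectiveness is the third study goal.

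**Working it through.** The article gives no cost, mammogram count or cost-effectiveness result, so there is no figure of its own to reproduce. What can be checked is when the conversion is valid and which way it can err.

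**1. Identity.** Within a window, mammograms per woman = (1 if at least one, else 0) + repeat mammograms. Between two arms of N women:

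extra mammograms = N × (difference in share + difference in repeats per woman).

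The conversion keeps only the first term.

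**2. Illustration.** Sample Size and Power gives N = 5,000 per arm and an expected difference of 3-5 points; I take 5. The incremental cost of 100,000 is my assumption, with cost and window matched. The conversion gives 5,000 × 0.05 = 250 and 100,000 / 250 = 400.

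| Difference in repeats per woman | Extra mammograms | Cost per mammogram |
|---|---|---|
| −0.01 | 5,000 × 0.04 = 200 | 500 |
| 0 | 5,000 × 0.05 = 250 | 400 |
| +0.01 | 5,000 × 0.06 = 300 | 333 |
| +0.05 | 5,000 × 0.10 = 500 | 200 |

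The converted 400 is right only in the second row.

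**3. Are women contacted inside the window?** In the mammogram-status table at study entry, 986 women were 18-23 months from their last mammogram. The columns from 18 months upward sum to 986 + 866 + 599 + 851 + 1,758 = 5,060, and 986 / 5,060 = 19.5%. At entry, then, about a fifth of the women with a recorded status past the trigger still counted as up to date.

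**4. Cost period.** Assume a steady screening interval of T months. The 24-month share is min(T, 24)/T. Mammograms per woman are 24/T in 24 months and 12/T in 12 months. Converted unit cost divided by true unit cost = gain in mammograms over the costed period / gain in share. Above 1 the conversion overstates the cost; below 1 it understates it.

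| Interval, before → after (months) | Gain in share | Gain in mammograms, 24 months | Ratio, 24-month costs | Ratio, 12-month costs |
|---|---|---|---|---|
| 30 → 24 | 0.200 | 0.200 | 1.00 | 0.50 |
| 36 → 30 | 0.133 | 0.133 | 1.00 | 0.50 |
| 26 → 22 | 0.077 | 0.168 | 2.18 | 1.09 |
| 23 → 20 | 0 | 0.157 | no finite value | no finite value |

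**5. Responders on a fixed cycle.** Assume a woman who would be screened every L months (or never) is instead screened every c months, with c = 21 or 19 (the trigger plus 3 or 1 months). Gain in share = 1 − 24/L; gain in mammograms per 24 months = 24/c − 24/L. For c = 21 and L = 30: 1 − 0.8 = 0.2; 1.143 − 0.8 = 0.343; ratio 1.71.

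| | L = 30 | L = 36 | L = 48 | never |
|---|---|---|---|---|
| c = 21, 24-month costs | 1.71 | 1.43 | 1.29 | 1.14 |
| c = 19, 24-month costs | 2.32 | 1.79 | 1.53 | 1.26 |
| c = 21, 12-month costs | 0.86 | 0.71 | 0.64 | 0.57 |
| c = 19, 12-month costs | 1.16 | 0.89 | 0.76 | 0.63 |

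With 24-month costs all eight cases exceed 1. With 12-month costs, as in a yearly comparison, seven of the eight fall below 1.

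The halving is a steady-state result. At the end of the first intervention year the look-back still covers twelve months before the interventions began, so it does not apply there, and the mismatch need not be the same in every year.

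**The case against.** The strongest reply is that little depends on the sentence. The committed result is cost per 1%, which is unaffected. The conversion is optional, called an estimate for a hypothetical sample, and given without a formula. A charitable reader could take an additional mammogram to mean one more woman on time. This stands as a limit on importance. It does not make the label correct, and none of the listed sensitivity analyses tests it: varying effectiveness by 5% or 10% changes the size of the effect, not its unit.

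A second reply is that the cost-effectiveness section does not state the window for its percentage of women with mammograms. That is true. The reference to on-time mammograms and the primary measure point to 24 months, but this is an inference. If a 12-month window were meant, an 18-month trigger would produce few second mammograms inside it, and share and count would nearly coincide.

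A third reply concerns a stronger conclusion that a reader might infer: that extra mammograms are undercounted and their unit cost overstated, by 14% to 132% on the 24-month rows of step 5. The protocol does not support this. Those rows need costs matched to 24 months, whereas comparisons are yearly. They need every responder to respond at every cycle, whereas the primary analysis section allows that interventions may lose effect with repetition. They ignore that RL women get the same letter at 18 months. A 19-month cycle is also close to the minimum for ETTC, where two two-week waits come before up to five call attempts. With equal repeats over a matched window the error is zero. This reply stands in full.

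**Conclusion.** The unit mismatch is real. As described, the conversion gives cost per additional woman with at least one mammogram in the window. Apart from chance cancellation, it equals cost per additional mammogram only if repeat mammograms per woman are the same in both arms and the cost period matches the outcome window. The plan states neither condition. The 18-month trigger and the repeat-intervention hypothesis cast doubt on the first, and yearly costing against a 24-month look-back casts doubt on the second.

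Sign and size are undetermined. The ratios above run from 0.50 to 2.32, with no finite value when only on-time women come back sooner. They rest on assumed steady intervals and show only that the error can go either way. They are not estimates for this trial. Nor does the article show whether the error would differ between RC and ETTC, since it has no interval data by arm.

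The point affects one optional restatement. It is worth correcting because that figure is aimed at adopters, but it does not touch the primary outcome or the main cost-effectiveness ratio.

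**What to change.** Label the converted figure as cost per additional woman with at least one mammogram in the past 24 months, and state the window used for the effect.

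If a cost per additional mammogram is wanted, do not derive it from the share. Divide the arm difference in cost by the arm difference in completed mammograms, with the same women as the base and mammograms counted over the same period as the costs. This settles the unit and the period together.

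The cost is a change of label and, for the second option, one extra count from mammogram dates already collected. The cost-per-1% result stays as planned.

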### Randomization

Patients joining the FCHP are automatically entered into our tracking system if they are female, aged 51-84, have a FC primary care provider and are in the plan for 24 months. Once identified and loaded onto the tracking system, they are automatically randomized to one of the three study arms. No blocking or stratification is used. The tracking database server uses a built-in T-SQL function to randomly allocate a number from 1-3 to each patient. The numbers refer to the specific intervention arm assignment. Documentation of the function can be found at: http://msdn.microsoft.com/en-us/library/ms177610.aspx

### Blinding

Since women receive different intervention depending on the arm to which they were randomized, blinding of subjects and the staff that receives and makes calls is not possible. Although a woman might reveal what type of contact she had had with study personnel in discussion with her PCP, PCPs are not informed as to which arm a patient is in. While the intervention assignment and the individual mammography outcome is not blinded, overall study arm outcomes will be blinded for all study personnel while the study is ongoing. The statistical team will conduct outcome analyses only at the conclusion of the intervention phase.

### Baseline results

Since July 2009, 18,509 female FCHP/FC enrollees aged 51-84 have been enrolled into our tracking database and were randomized into one of three arms. Table 6 shows their mammogram status at randomization. Table 7 shows the characteristics of the study sample, their approval or non-consent status by age. At baseline, 5,223 women were eligible for an intervention.

**Table 6 T6:** Mammogram Status at Study Entry*

Last Mammogram	<8 mo. ago	18-23 mo. ago	24-29 mo. ago	30-35 mo. ago	26-48 mo. ago	>48 mo. ago
N = 18,509 (100.0%)	12,808 (69.20)	986 (5.33)	866 (4.68)	599 (3.24)	851 (4.60)	1,758 (9.50)

* Columns do not total to 100% because of missing data

**Table 7 T7:** Characteristics of Study Sample

Age	Eligible women at baseline in study database*	Women opted out of intervention phase after broadcast letter	PCP approved for possible intervention phase	Women opted out of intervention phase at 1^st ^intervention attempt	Women eligible for reminder intervention study	Women >= 18 months from last mammogram and intervention eligible
50-59	5,901 (31.88)	30 (3.44)	5,826 (33.62)	12 (20.69)	5,814 (33.66)	1,842 (35.27)

60-69	4,781 (25.83)	115 (13.17)	4,613 (26.62)	13 (22.41)	4,600 (26.63)	1,146 (21.94)

70-79	5,429 (29.33)	494 (56.59)	4,818 (27.80)	15 (25.86)	4,803 (27.81)	1,329 (25.45)

80-84	2,398 (12.96)	234 (26.80)	2,074 (11.97)	18 (31.03)	2,056 (11.90)	906 (17.35)

Total	18,509	873	17,331	58	17,273	5,223

*All women 50-84 in FCHP for ≥24 months with current FC PCP and no mammogram in last 4 months

## Discussion

The interventions we will evaluate and compare in this study represent system solutions to reminding, scheduling, counseling and motivating women to get regular repeated mammograms. These interventions represent an effort to remove much of the reminder/counseling burden from PCPs and their practice staff. In particular, we are interested in evaluating the effectiveness of a centralized reminder and counseling system as alternative to the primary care providers' (PCPs) role in reminding, educating and/or motivating women to get screening mammography. While many women may be brought to regular on time screening with minimal reminders, women who are significantly overdue for screening or habitually non-compliant need more than reminders. We believe counseling and motivating these women will be required. Unfortunately, providers have not been consistently involved in lengthy education or counseling the more reluctant women due to time constraints, limited patient responsiveness, limited PCP training in counseling and limited reimbursement for providing preventive services [58]. Even when providers undertake counseling, it may be brief, incomplete and/or relatively ineffective due to limited time and training [59-63]. All these problems are compounded by the fact that the numbers of new physicians entering primary care are decreasing significantly and the need for physician extenders is increasing [64]. Finding cost-effective ways to complement PCPs recommendations is critical and the results of this study will be illuminating. In addition, since this study aims to identify the most effective and most cost effective of the outreach strategies, the forthcoming result will provide much needed and timely guidance for health plans [1] and ACOs.

Since the intervention period will span 48 months, we will be able to evaluate the effect of repeated interventions more fully than others have [53]. We hypothesize that woman who respond to an initial intervention may, when coming due for another mammogram, either requires no intervention or a less intense intervention than they responded to initially.

## List of Abbreviations

ACOs: Accountable Care Organizations; CATI: Computer assisted telephone interview; CEA: Cost effectiveness analysis; EPICS: Empowering Physicians to Improve (Breast) Cancer Screening; ETTC: Enhanced tailored telephone counseling call; FC: Fallon Clinic; FCHP: Fallon Community Health Plan; HEDIS: Healthcare Effectiveness and Data Information Set; PAPM: Precaution Adoption Process Model; PASS: Power Analysis and Sample Size; PCP: Primary Care Provider; RC: Reminder call; RL: Reminder letter; TTC: Tailored telephone counseling
